#### 3.2.2. Sweets, Sugar, and Honey

Limiting the consumption of sweets, sugar, and honey including high-sweetened jam and fruits candied (once a week or less) is recommended, as these foods are a source of monosaccharides and many of these foods contain a large amount of saturated fatty acids and trans-isomers of unsaturated fatty acids. This recommendation is in line with the recommendations for the general population (no precise cut-off for Poles was given) to prevent obesity, diabetes, and other diseases, including cancers [27,28,29]. It should be underlined that the risk of the development of diabetes is greater in HT patients than people without thyroid diseases. Although the autoimmune character of the HT predisposes to type 1 diabetes, pro-inflammatory cytokines also have an influence on receptor insulins, which can lead to impairment of their function and the development of insulin resistance and type 2 diabetes [13]. 

#### 3.2.3. Sweetened Beverages and Energy Drinks

Limiting the consumption of sweetened beverages energy drinks (once a week or less) regardless of the sweeteners type (sugar, glucose–fructose syrup or artificial sweeteners, etc.) is recommended. Sweetened beverages can affect hormonal levels in the blood by increasing T4 and parathyroid hormones, and lowering T3 and aldosterone levels [78]. Abbott et al. [22] recommended the elimination of foods with low nutritional value (sugar-sweetened beverages, ultraprocessed foods, etc.), and foods that could result in an aberrant immune response via dysregulated antigen presentation or detrimentally affect both the gut microbiome and the integrity of the gastrointestinal barrier. Animal studies report that artificial sweeteners affect the immune system and show that sucralose diminishes the thyroid axis activity [79]. Energy drinks, regardless of whether they are standard or low-calorie drinks, commonly contain sugar substitutes such as saccharin, aspartame, sucralose, acesulphame K, and neotame. Clinical reports show that the intake of artificial sweeteners may play a role in AITD and lead to increased TSH [79].

#### 3.2.4. Fast Food

Limiting the consumption of fast food (once a week or less) is recommended. The recommendation for the general population is to avoid fast food [27,28,29]. There is a growing, alarming trend of fast food consumption associated with a worsening of cardiometabolic outcomes, including obesity [80]. It was reported that the consumption of fast foods ≥2 times/week increased the risk of insulin resistance [81]. In adults, every one-meal/week increase in fast food and sit-down restaurant consumption was associated with an increase in BMI [82].

#### 3.2.5. Soybean and Millet

Soybean and millet—e.g., soya: seeds, sprouts, tofu, milk; millet groats—are controversial foods. Limiting the consumption of these foods (twice a month or less) is recommended, despite the potential human health benefits of soy in the prevention of cancer, cardiovascular diseases, the reduction of menopause symptoms, increased bone-mineral density, and decreased insulin resistance [83]. Conversely, soy has raised concern about thyroid gland function [84]. According to Messina et al., the literature provides little evidence that the consumption of soy foods or isoflavones has adverse effects for euthyroid individuals with iodine deficiency. However, there is a theoretical concern based on in vitro and animal studies that individuals with impaired thyroid function and/or whose iodine intake is marginal are more likely to develop hypothyroidism with soy consumption [85]. Thus, it is vital that consumers of soy-based foods be sure that their iodine intake is adequate. In addition, soy may hinder the absorption of thyroid drugs [84].

#### 3.2.6. Alcohols

Limiting the consumption of alcohol (once a month or less) is recommended. However, the recommendation for the general population is not to consume alcohol [27,28,29]. Moderate alcohol consumption has been shown to have a protective role in the development of the HT [86,87], while regular alcohol use did not change TPO-Ab, but may risk HT hypothyroidism [86]. A population-based case-control study in Denmark likewise observed that moderate alcohol consumption reduced the risk of overt autoimmune hypothyroidism: ORs were 1.98 (95% CI, 1.21 to 3.33) for 0 alcoholic units/week, 1.00 for 1 to 10 units/week (reference), 0.41 (95% CI, 0.20 to 0.83) for 11 to 20 units/week, and 0.90 (95% CI, 0.41 to 2.00) for ≥21 units/week [88].

### 3.3. Strengths and Limitations

The strength of the study was the development of a simple dietary protocol with a user-friendly approach that is easy to use for both individuals with HT and health professionals. This dietary protocol was developed based on scientific evidence and presents the best adherence to current knowledge. Simple markers of adiposity (BMI, WHtR) and metabolic parameters (FBG, TG, TC) useful in dietetic counseling and clinical practice (and easy to replicate in other studies) will be applied. In addition, advanced methods of adiposity measurement (bioelectrical impedance analysis method with an SECA mBCA 525 analyzer) will be applied to accurately measure body composition, including fat mass and skeletal muscle mass. Since the data are experimental observations, the causal effect of dietary intervention can be demonstrated. 

The main limitation is that the study will not have a controlled placebo as there is no ‘dietetic placebo’ for dietetic counseling. Therefore, the graphic–text tool will be controlled with conventional dietetic management. Secondly, the study is not double-blinded because (i) the researcher who will be involved in dietetic counseling will be aware of which participants are included in the QDP group and which participants are in the CDC group, and (ii) it is possible that respondents may be aware of what dietetic counseling they are following. The next limitation is the use of non-thyroid-specific food frequency questionnaires (FFQs) to describe diet quality. Both FFQs have been previously used to study the association between diet and health outcomes in the context of non-alcoholic fatty liver disease [89], celiac disease [90], metabolic syndrome [91], breast and lung cancers [92,93], and are accurate tools to describe overall diet quality as well as negative (nHDI) or positive (pHDI) aspects of diet quality. Unfortunately, both FFQs do not contain any detailed specification of food items that are important (more or less recommended for consumption) in the ‘Hashi diet’ (e.g., buckwheat grain or cruciferous vegetables). This limitation will be reduced by a quantitative (in points) assessment of the consumption frequency of those foods, which was recorded in real time via a self-monitoring diary, to assess adherence to the QDP. Further limitations can be attributed to using FFQs. Although there is evidence of many advantages related to data collection with the FFQs, several shortcomings have been reported, e.g., the data relies heavily on memory; therefore, declining cognitive ability may result in errors when reporting on food frequency consumption; the food list cannot cover all the foods consumed by respondents, which may lead to underreporting; and the use of a questionnaire causes some uncertainty due to social desirability bias, especially in females, who may provide more socially acceptable answers [94]. To describe sedentary (screen time) and active behaviors (at leisure time and work), a questionnaire with simple questions will be used. This will allow respondents to be ranked into categories of low and high physical activity levels, but will not allow precise measurement of physical activity. Office measurements of blood pressure will be taken, so ‘white coat’ hypertension phenomena should be taken into account when elevated blood pressure is interpreted [42,43]. Future studies should consider applying other methods to fully describe subjects’ dietary behaviors (e.g., biomarkers and/or repeated food records) and measure physical activity (e.g., accelerometry) instead of self-reported data [94,95] and also implement repeated blood pressure measuring (e.g., 24-hour monitoring) [42,43]. 

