### 1.1. Research Objective and Hypothesis

The current state of knowledge related to diet in HT is far from satisfactory, while many HT subjects experience many disorders and report reduced quality of life [13,14,18,23]. There is a strong need to summarize the evidence and develop dietary recommendations that are simple for HT subjects to understand and implement daily over a long-term period, and are useful for dieticians and other health professionals. The conventional approach to dietetic counseling is a structured process aimed at supporting individual patients to modify their dietary behaviors to improve health outcomes [24]. Conventional dietetic counseling is based on the development of individual recommendations and formulating detailed guidelines, which may prove difficult for patients to follow over the long term due to growing fatigue, lowering of motivation, the time required, and difficulties maintaining subject compliance to the diet [25]. Mitchell et al. [24] reported that dietetic counseling appears to be effective, e.g., in improving diet quality, diabetes outcomes, and weight loss outcomes, while limited evidence was found for the effectiveness of direct dietetic counseling alone in achieving outcomes relating to plasma lipid levels and blood pressure. The authors suggested that future research might explore novel nutrition counseling approaches.

There are three aims of the study: (1) to develop a qualitative dietary protocol (QDP; ‘Diet4Hashi’) as a simple, graphic–text tool dedicated TH subjects, (2) to evaluate the use of the QDP in dietetic counseling compared to conventional dietetic counseling (CDC) in HT women, (3) to assess the impact of both the QDP and the CDC on diet quality, quality of life, adiposity, and metabolic parameters. It is planned to develop a food-only protocol without considering the use of supplements because an adequate, well-balanced diet should be the first step in a dietary approach to improving health.

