### 1.2. Study Design

The study is designed as a single-center dietary intervention lasting six months, with a random allocation of HT women into two parallel groups: experimental and control. In the experimental group, the QDP will be applied, while the CDC will be applied in the control group. The QDP is based on subject self-monitoring supported with a graphic–text tool to help them in food selection and adequate food frequency consumption, while the CDC will be supported by an oral explanation and printed sample menus given by dietician. Both approaches include the same dietary recommendations for HT, extracted from the literature, but differ in subject–dietician cooperation. 

The schedule of the enrolment, intervention, and data collection is presented in Table 1. All data will be collected at the same time for both groups, with one exception. The experimental group, supported with a graphic–text tool, will be asked to complete self-monitoring diaries during the six months of the study.

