### 2.2. Participants Selections

The participants will be recruited for the study through ads in the press, via the Internet and by e-mail invitation between October and December 2019. Approximately 140 women with HT are expected to respond to the invitation letter (describing the details of the planned trial) and will be screened for eligibility (Figure 1). All visits for data collection will take place at the Department of Human Nutrition (Center of Gastronomy with Dietetics and Food Bioassessment), Faculty of Food Science, University of Warmia and Mazury in Olsztyn. The trial starts in winter months, and all subjects will be advised to continue their long-term vitamin D supplementation. 

To take part in the study, the participants have to be prior diagnosed as having HT according to the American Thyroid Association guidelines [26] and have a medical certificate for levothyroxine or other thyroid hormone treatment (e.g., levothyroxine plus liothyronine). The participants will be required to show a medical diagnosis with thyroid ultrasonography and the results of thyroid function tests carried out no later than two months before enrolment. Detailed inclusion and exclusion criteria are presented in Table 2. Information collected at the interview, which not will be used as including/excluding criterion, is the age at which HT was diagnosed, the use of dietary supplements in the past, the dose of levothyroxine or other thyroid hormones in current treatment, and hormone status (menstruating: yes, no, irregular). Elevated serum auto-antibodies against thyroid peroxidase and thyroglobulin will be recorded but will not be used as excluding criterion.

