### 2.4. Dietary Intervention with QDP and CDC

Both dietetic approaches (QDP and CDC) are based on the same dietary recommendations in HT. To identify studies reporting dietary recommendations in HT or hypothyroidism (reviews) and investigations on diet and health outcomes in HT or hypothyroidism (original papers), the PubMed, Embase, and Cochrane Library databases (to March 2019) and the bibliographies of key articles were searched. Based on the data extracted, dietary recommendations for HT were established. Justification for these recommendations is presented in detail in the discussion (Section 3.1 and Section 3.2). 

General dietary guidelines for HT subjects will be distributed as a printed leaflet, which was the same for all participants in both the QDP and CDC groups (Table S1, in Polish: Table S2). In the leaflet, there are universal dietary guidelines which, if adhered to, may reduce the risk of health disorders. Similar pro-healthy dietary guidelines are widely promoted for the general population [27,28,29]. 

In the CDC group, dietetic counseling will be conducted in a conventional manner. Respondents will receive detailed oral explanations and printed sample menus given by a dietician. In this model of subject–dietician cooperation, the dietician is more involved while the subject is less (being more passive).

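### Both arms get the same dietary recommendations, so randomisation identifies only the effect of the QDP format relative to CDC, while aim 3, part of hypothesis 2 and the causal sentence in section 3.3 claim more

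*Protocol article*

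**What the plan says.** Section 1.2 describes two randomised parallel groups ("with a random allocation of HT women into two parallel groups: experimental and control") and adds: "Both approaches include the same dietary recommendations for HT, extracted from the literature". Section 2.4 repeats this ("Both dietetic approaches (QDP and CDC) are based on the same dietary recommendations in HT") and says of the general leaflet that it "which was the same for all participants in both the QDP and CDC groups". The arms differ in how subject and dietician work together: a graphic–text tool with a self-monitoring diary in QDP, oral explanation and sample menus in CDC. Neither section 1.2 nor Table 1 contains an arm without the recommendations.

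The claims are broader than that contrast. Aim 3 in section 1.1 is "to assess the impact of both the QDP and the CDC on diet quality, quality of life, adiposity, and metabolic parameters", listed separately from aim 2, which already covers QDP against CDC. The first part of hypothesis 2 expects a well-composed diet supported by the QDP to improve quality of life, adiposity and metabolic parameters. Superiority over CDC follows only as a possibility. Section 3.3 says, without qualification: "Since the data are experimental observations, the causal effect of dietary intervention can be demonstrated".

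For continuous outcomes, section 2.12 examines change from baseline with a t-test for dependent samples when the data are normal. Section 2.2 places recruitment in October to December 2019 and says: "The trial starts in winter months, and all subjects will be advised to continue their long-term vitamin D supplementation".

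**The concern.** A causal statement is as wide as the contrast that was randomised. Here that contrast is the counselling format. Whether the recommendations work, or whether either form of counselling works in absolute terms, can only be read from before-after change within an arm. That change also contains whatever else shifts between the two visits, including season and the course of treated disease.

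The practical risk lies in the result where both arms improve by about the same amount. The design cannot then distinguish two effective approaches from two arms drifting together, yet aim 3 and the causal sentence leave room to credit the diet. The named paired test gives that reading a planned route into the results, in a report meant for dieticians and physicians.

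**Working it through.** **Step 1. What randomisation identifies.** Write the mean change in each arm as

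- QDP: common change over time + effect of shared recommendations + effect of QDP format
- CDC: common change over time + effect of shared recommendations + effect of CDC format

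The difference is effect of QDP format − effect of CDC format. (If the effect of the recommendations depends on the format that delivers them, that part counts with the format.) The first two terms cancel. They cannot be separated from each other in either arm, because no arm receives the first without the second.

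**Step 2. Claims set against that contrast.**

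| Place | Quantity claimed | Identified by randomisation? |
|---|---|---|
| Aim 2 and hypothesis 1 (1.1) | QDP against CDC | Yes |
| Aim 3 (1.1) | Impact of each arm | No |
| Hypothesis 2, first part (1.1) | Improvement with diet plus QDP | No |
| Hypothesis 2, last sentence (1.1) | QDP better than CDC | Yes |
| Causal sentence (3.3) | Dietary intervention, unspecified | Only if it means QDP against CDC |

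**Step 3. Timing.** Recruitment in October to December with a start in winter (2.2) and a last visit at six months (1.2, Table 1) puts every baseline in autumn/winter and every final visit in spring/summer. No staggered entry would let season average out.

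**Step 4. Planning figures.** Section 2.11 assumes decreases of 20/10 points in overall quality of life (QDP/CDC), 5% significance, 80% power and 50 per arm including 20% drop-out. It gives no SD, so the sample size cannot be reproduced forward and the SD has to be back-solved:

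- Completers per arm: 50 × 0.8 = 40. Assumed difference: 20 − 10 = 10 points.
- Normal approximation: SD = 10 × √(40/2) / (1.960 + 0.842) = 44.72 / 2.802 ≈ 16.0 points.
- With the t distribution: standardised difference 0.634, so SD = 10 / 0.634 ≈ 15.8 points.

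Both are about 16. The figure is implied, not stated.

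**Step 5. Illustration of the within-arm test.** Suppose neither approach has any effect and all women drift by a common amount. The drift sizes are assumptions; the documents give none. A paired t-test on 40 women has noncentrality drift × √40 / SD and a two-sided 5% critical value of 2.02 (39 df). With SD 15.8:

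| Assumed common drift (points) | Noncentrality | One arm significant |
|---|---|---|
| 3 | 1.20 | 22% |
| 5 | 2.01 | 50% |
| 10 | 4.01 | 97% |

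With SD 15.96 the results are 21%, 49% and 97%. In a simulation of 20,000 trials at SD 15.96, drifts of 0, 5 and 10 points made both arms significant in 0.2%, 23% and 94% of trials. The between-arm test rejected in 5% each time.

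For BMI, 42 × 0.8 = 33.6 completers and a difference of 1.0 kg/m² imply an SD of about 1.46 kg/m². With 33 completers, assumed common drifts of 0.25, 0.5 and 1.0 kg/m² give one-arm significance in 16%, 48% and 97%.

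**The case against.** The strongest reply is that the causal sentence can be read correctly. Section 1.2 uses the term dietary intervention for the whole two-arm randomised study, and on that reading the sentence refers to QDP against CDC and is right. That stands: the sentence is too broad rather than plainly false. It does not rescue aim 3 or the first part of hypothesis 2, which speak of effects within an arm.

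Second, the randomised question is already in the plan. Aim 2, hypothesis 1 and the end of hypothesis 2 state it, section 2.11 is built on the expected difference between groups, and section 2.12 says differences between groups will be verified. This also stands, and it is why the trial's main comparison is not in doubt. But the parametric test that section 2.12 names for change is the paired one.

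Third, section 3.3 names the missing placebo as the main limitation and says the tool is controlled with conventional management. This concedes much of the point. It does not limit the causal sentence, does not say that the effect of the shared recommendations is unidentified, and does not mention season.

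A reader might go further and infer that the plan would report twice the true effect, since 20 points in QDP is double the 10-point difference. The documents do not support this. The doubling holds only if the target is QDP minus CDC. For diet against no diet the true effect is unknown, and the 10 points assumed for CDC could be entirely real. A reader might also infer regression to the mean among women answering advertisements. Table 2 sets no threshold for poor quality of life, and its BMI limits exclude women below 18.5 or at 35 kg/m² and above rather than select for high values. That remains speculation.

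**Conclusion.** The concern holds in a limited form. Two arms sharing the same recommendations and leaflet identify the effect of the QDP format relative to CDC and nothing wider. Aim 3, the first part of hypothesis 2 and the unqualified causal sentence go beyond this, and the paired test could support them only with before-after evidence collected from one season into another. The conclusion follows from the design and does not depend on the numbers. Those are illustrative and rest on a back-solved SD of about 16 points, 40 completers per arm and assumed drifts.

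The documents do not support reading this as a failed design or as proof that diet effects will be misreported. An active comparator is a legitimate choice, the between-arm comparison is valid, and no passage says that equal improvement will be taken as efficacy. This is a correction of wording and of the designated test that is worth making. It is not a fault that puts the trial's main comparison at risk.

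**What to change.** 1. In section 3.3, replace the causal sentence with one to this effect: the randomised comparison can show the causal effect of the QDP format relative to CDC; the effect of the dietary recommendations, which both arms receive, is not identified.
2. Make the between-arm comparison of six-month change the test for the efficacy part of aim 3 and for hypothesis 2, and say so in section 2.12.
3. Report within-arm changes with 95% confidence intervals as descriptive only, noting that they run from an autumn/winter baseline to a visit six months later and that there is no untreated control. Draw no efficacy conclusion from them.

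The cost is rewording in sections 1.1, 2.12 and 3.3. Arms, outcomes, visits and sample size stay as they are, and no further women or data are needed. The downside is a narrower claim: the trial could then say which counselling format does better, but not how much the diet itself achieves.

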
## 4. Conclusions

Due to the development of an easy-to-follow qualitative dietary protocol for HT subjects (Diet4Hashi), this study will contribute to providing valuable data for dieticians and physicians. It is anticipated that this graphic-text qualitative dietary protocol, by improving food selection and diet quality, can reduce adiposity and improve metabolic parameters and the quality of life of HT women. Further investigations are needed to verify the use of this dietary protocol in HT males. 

